
#### Sham acupuncture group

Subjects in the sham acupuncture group will undergo the same procedures as those in the sinew acupuncture group except that the non-insertion sham acupuncture will be applied. Briefly, subjects will sit in a chair and their vision of their knees will be blocked by the trolley table. After disinfection, sterile needles with a size of 0.30 mm × 40 mm (MOCM ®) will be used to slightly puncture the acupoint without passing through the skin. The needles will immediately be covered with non-allergenic bandages to ensure sufficient blinding.

### Outcome measures

The VAS at week 4 will be the primary outcome. The WOMAC, TUG, 8-step SCT, and SF-36 scores will be the secondary outcomes. The assessment schedule is shown in Table 1. Independent assessors who are not involved in acupuncture treatments will perform the VAS assessments (asking subjects to indicate the pain intensity at the most painful points during walking and ascending/descending a step and overall). Acupuncturists will complete a “Physical Examination and Treatment Form” including details of the medical history, diagnosis and treatment procedures. The acupuncturists will communicate with the subjects using neutral language. The administration of analgesics, external ointments and herbal medicines and the time of daily exercises will be collected weekly from patient diaries during the intervention period and at each visit during the follow-up period.

**Table 1 Tab1:** The schedule of enrollment, interventions, and assessments

Items	Enrollment	Allocation (baseline)	Interventions (± 2 days)										Follow-up	
Time points (week)	-2	0	1			2			3		4		6	10
Treatment sessions (n)	–	–	1	2	3	4	5	6	7	8	9	10	–	–
Eligibility screen	✓													
Informed consent	✓													
VAS		✓	✓	✓	✓	✓	✓	✓	✓	✓	✓	✓	✓	✓
WOMAC		✓			✓			✓		✓		✓	✓	✓
SF-36		✓										✓		✓
TUG		✓						✓				✓	✓	✓
8-step SCT		✓						✓				✓	✓	✓
PE & Tx		✓	✓	✓	✓	✓	✓	✓	✓	✓	✓	✓	✓	✓
Patient Diary					✓			✓		✓		✓	✓	✓
Credibility Test								✓				✓		
Test of Blinding Success												✓		
Adverse events			✓	✓	✓	✓	✓	✓	✓	✓	✓	✓	✓	✓

PE & Tx, Physical Examination and Treatment Form; SCT, stair climb test; SF-36, 36-item short form; TUG, timed up & go test; VAS, visual analog scale; WOMAC, Western Ontario and McMasters University Osteoarthritis Index

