### Exclusion criteria

Subjects will be excluded if they meet any of the following criteria: (i) are unable to walk; (ii) have a serious infection of the knee; (iii) have suspected tears in any ligaments or menisci or acute inflammation of the synovial capsule; (iv) have a history of trauma, ligament damage, fracture, or surgery on the knee(s) within 6 months, causing pain or functional problems (history of knee replacement will be excluded); (v) have a history of local tumour/malignancy at the knee; (vi) have physical or laboratory findings indicating infection, presence of autoimmune disease or inflammatory arthritis; (vii) have knee pain caused by radiculopathy/herniation of an intervertebral disc; (viii) have end-stage diseases or other suspected severe conditions such as deep vein thrombosis of the lower limb, oedema related to cancer or cancer treatment, severe blood coagulation disorders, uncontrolled systemic arterial hypertension and severe diabetes; (ix) have a history of prolotherapy, hyaluronic acid injections or corticosteroids injections within 3 months; (x) have received acupuncture, electro-acupuncture, Tui-na therapy, massage, or physiotherapy 8 weeks prior to enrolment in the trial; (xi) have severe pain in other regions; (xii) have severe mental disorder(s); (xiii) are oversensitive to needles; and (xiv) are insensitive to pain due to advanced diabetes, neuropathy or use of strong painkillers.

Eligible subjects will receive baseline assessments and will be randomly allocated to the sinew acupuncture group (*n* = 43) or the sham acupuncture group (*n* = 43) in a ratio of 1:1 by block randomization. The random digits and letters will be generated by SPSS, covered by aluminium foil, and sealed into opaque envelopes.

Subjects will be advised not to receive other acupuncture treatments, Tui-na, massage or physiotherapy. Subjects are not restricted from the use of painkillers (including herbs) or external ointments if they suffer intolerable pain. The use of rescue medications, the daily level of morning stiffness and exercise time will be recorded in patient diaries.

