### Data analysis

All data will be doubly entered into a password-protected computer 1 week after data collection. The statistical analysis will be performed by SPSS 22.0 for Windows by a single statistician. The scores will be analysed by the intent-to-treat analysis. The last observation carried forward method will be used for missing data. Comparisons of continuous variables between the acupuncture and sham groups will be assessed using Student’s t-test or analysis of covariance (ANCOVA) with baseline measures as covariates. Comparisons of categorical data between groups will be tested by the χ^2^ test or the Mann–Whitney U-test. Changes in the scores from baseline within treatment groups will be assessed by the paired t-test or the Wilcoxon signed ranks test. Data from the patient diary will be assessed to analyse covariate balances in the two groups. If we find an imbalance, we will use the propensity score method [31] or the conditional inference method [32] to remove the confounding effect. All statistical tests will be two-sided at a 5% significance level.

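### The patient diary starts only after randomisation, so the planned diary-based covariate balance check, and the adjustment it triggers, have no pre-randomisation value to rest on

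*Protocol article*

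**What the plan says.** The content of the diary is set out under Exclusion criteria: "The use of rescue medications, the daily level of morning stiffness and exercise time will be recorded in patient diaries". Outcome measures adds ointments and herbal medicines and fixes the timing: the data "will be collected weekly from patient diaries during the intervention period and at each visit during the follow-up period".

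The "Patient Diary" row of Table 1 matches that sentence. It is ticked at sessions 3, 6, 8 and 10 and at weeks 6 and 10. Its enrolment (week -2) and baseline (week 0) cells are empty.

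Painkillers are allowed on a condition: "Subjects are not restricted from the use of painkillers (including herbs) or external ointments if they suffer intolerable pain".

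The use of the diary is given under Data analysis: "Data from the patient diary will be assessed to analyse covariate balances in the two groups". The consequence follows: "If we find an imbalance, we will use the propensity score method", with conditional inference as the alternative, in order to take out confounding.

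**The concern.** Covariate balance and confounding describe the state of the two arms at entry. Every diary value in the schedule is collected after allocation, when treatment may already have changed it. A patient whose pain falls may take fewer painkillers, use less ointment or exercise more.

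Suppose the sham arm reports more painkiller use in weeks 1-4. It may have held heavier users from the start, or its patients may have taken more because their pain was less well relieved. The first is a chance imbalance that can sensibly be adjusted for. The second is a consequence of allocation, and adjusting for it could remove part of the effect that the trial sets out to measure. The plan would treat both alike.

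The question will be asked, because the primary outcome is a pain score and rescue use is permitted. An analysis plan written later cannot supply a baseline that was never collected.

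**Working it through.** **1. Is the empty baseline cell deliberate?** VAS, WOMAC, SF-36, TUG, the stair climb test and the Physical Examination and Treatment Form are all ticked at week 0 in Table 1; the diary is not. The text under Outcome measures gives the same window. The two sources agree, so this is not a broken table.

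**2. Could the diary have been collected before allocation?** The order is stated: "Eligible subjects will receive baseline assessments and will be randomly allocated to the sinew acupuncture group". Table 1 also has an enrolment contact at week -2. Two contacts before allocation therefore exist already.

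**3. Is there another baseline source?** The Physical Examination and Treatment Form is completed at week 0, "including details of the medical history, diagnosis and treatment procedures". Analgesic quantity, ointments, herbs and exercise time are not named.

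**4. Number per arm.** The plan's 37 per group can be reproduced. With d = 7.16/10.7 = 0.669, two-sided alpha 0.05 and power 0.80, the t-test needs 36.04, so 37. Then 37 x 1.15 = 42.55, so 43, the number per arm given with the allocation. (The last sentence of Sample size estimation puts 86 in each group; the abstract and the allocation statement give 86 in total. I use 43.)

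**5. How large an entry difference can chance produce?**

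Continuous item, such as exercise time: the SD of the difference in means is sqrt(2/43) = 0.216 SD, and 1.96 x 0.216 = 0.42 SD. The probability of a difference of at least 0.3 SD is 2 x [1 - Φ(0.3/0.216)] = 0.16.

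Yes/no item, such as any painkiller use: let X and Y be independent Binomial(43, p) and compute P(|X - Y|/43 ≥ t) exactly. The documents give no rate of use at entry, so p is assumed.

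| p (assumed) | ≥ 10 points | ≥ 15 points | ≥ 20 points |
|---|---|---|---|
| 0.2 | 0.22 | 0.08 | 0.02 |
| 0.3 | 0.29 | 0.13 | 0.05 |
| 0.4 | 0.32 | 0.15 | 0.06 |
| 0.5 | 0.33 | 0.16 | 0.07 |
| 0.6 | 0.32 | 0.15 | 0.06 |

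This is ordinary chance variation under randomisation. It shows only that a moderate entry difference is plausible and that the diary as scheduled could not reveal it.

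**6. What would a baseline add to diary comparisons?** With correlation r between baseline and on-treatment values, ANCOVA multiplies the variance of the arm difference by 1 - r². For r = 0.5 this is 0.75 (25% less) and for r = 0.7 it is 0.51 (49% less). These values of r are assumed; the documents give none.

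**The case against.** The strongest reply is that randomisation makes any entry difference a matter of chance, and that the standard error of the between-arm comparison already allows for it. This stands. A reader might infer that the primary VAS result is biased by the missing diary baseline. It is not: the unadjusted comparison is unbiased, and VAS has its own week 0 value. No sample size, alpha or power figure changes.

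Four other strong readings go further than the document does:

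- **Drug use at entry is wholly unrecorded.** The medical history may capture some of it, and the exclusion for insensitivity to pain requires asking about strong painkillers. Morning stiffness has related entry data in the inclusion criteria and the WOMAC stiffness items. The content of case report forms is also something an article may leave out. What the document does show is that no diary value precedes allocation, and that no other form is said to cover the same items.
- **The plan promises baseline-adjusted analysis of diary items.** Data analysis names a t-test or ANCOVA, and diary items are not among the listed primary and secondary outcomes. No commitment is broken.
- **Co-medication is freely allowed.** The permission is tied to intolerable pain.
- **The fortnight before allocation is idle.** It may be needed for radiographic and other screening, and its length in practice is not stated.

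A further objection is that a baseline diary does not by itself make adjustment for on-treatment use valid. That is correct, which is why the balance check and any adjustment must also move to the pre-randomisation values.

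**Conclusion.** The point holds in limited form. The diary is scheduled only from week 1, yet it is to supply the covariates for a balance check and, if that fails, for an adjustment. Values that treatment can change cannot serve that purpose. Three things suffer: the balance check, the adjustment it triggers, and the interpretation of painkiller, ointment, herb and exercise data.

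For scale, a chance entry difference of up to about 0.42 SD in a continuous item is within the 95% range. A gap of at least 10 points in the proportion of users has probability 0.22 to 0.33 if 20% to 60% use the item at entry (assumed). How much of the VAS effect a mistaken adjustment would remove cannot be calculated from the document. The 25-49% gain in precision rests on an assumed correlation and applies to diary variables, not to the primary VAS. This is an inexpensive improvement to make before enrolment, not a threat to the primary inference.

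**What to change.** Issue the existing diary at the week -2 enrolment visit and collect it at week 0 before allocation. Add the matching ticks to Table 1 and amend the collection sentence in Outcome measures.

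In Data analysis:

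- base the covariate balance check, and any propensity-score or conditional-inference adjustment, on the pre-randomisation diary values only;
- use those values as the baseline covariate when diary items are compared between arms;
- report diary use after allocation descriptively or as an outcome, not as a covariate to be balanced.

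The cost is up to about two extra diary weeks per enrolled subject, including those later found ineligible. No new visit or instrument is needed. If screening takes less than two weeks, use the days available. The change must be made prospectively; it cannot be recovered for subjects already randomised.

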### Measurement instruments

The 0–100 mm VAS is used to measure pain intensity. Subjects will indicate pain intensity on the VAS, with 0 mm representing no pain and 100 mm representing the most intolerable pain. Pain intensity will be measured at the most painful point during walking, the most painful point during ascending and descending a step, and the overall pain before and immediately after every treatment session and at follow-up at week 6 and week 10.

The WOMAC (Hong Kong Cantonese Version) [10] will be completed by subjects and will assess three domains: pain (5 items), stiffness (2 items) and physical function (17 items). The WOMAC will be measured at baseline, every week for the first 4 weeks, week 6 and week 10.

The SF-36 (Hong Kong Cantonese version) will be used to assess general QOL. The QOL will be collected by assessors at baseline, week 4 and week 10.

TUG and 8-step SCT will be evaluated by assessors at baseline, every 2 weeks after the last treatment session, and at week 6 and week 10.

### Assessment of credibility

The Credibility of Treatment Rating Scale will be used to assess the credibility of the acupuncture treatments after the 6th treatment at week 2 and the last treatment at week 4. The 4-item scale is specifically designed to assess the credibility of acupuncture. The following questions will be asked to each subject by the assessors: (1) Do you believe this treatment will reduce the pain you are suffering? (2) Would you recommend this treatment to a friend or relative with the same problem? (3) Does the treatment seem to be a logical one? (4) Do you believe this treatment could be very effective in curing your knee osteoarthritis? [30].

### Assessment of blinding success for acupuncture treatment

The blinding success of subjects will be evaluated by assessors after the last treatment session at week 4. Subjects in both groups will be asked the following question: “When you volunteered for the trial, you were informed that you had an equal chance of receiving sinew acupuncture or sham acupuncture treatment. Which acupuncture do you think you received?” Three options will be provided to the subjects, sinew acupuncture, sham acupuncture, and uncertain. Those who answered either sinew acupuncture or sham acupuncture will be asked to provide a reason for that assumption; the results will be recorded [12].

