## Discussion

KOA is one of the most common diseases among the elderly. This study will evaluate the efficacy of sinew acupuncture for pain reduction, functional movement improvement, and QOL improvement in KOA patients. In our clinic, there are 8–10 new KOA patients each month. We estimate that recruitment will be completed in 10 months.

The study is conducted in collaboration with the School of Chinese Medicine, Department of Diagnostic Radiology and Department of Orthopaedics & Traumatology, Li Ka Shing Faculty of Medicine, HKU. The eligibility of KOA subjects will be assessed by clinical physicians. The intervention will be performed by experienced acupuncturists. The subjects and assessors will be blinded to subjects’ allocations. The acupuncturist will not be involved in assessments or data entry. Data will be analysed by an independent statistician.

In acupuncture RCTs, it is critical to choose an appropriate control population. Vickers AJ et al. found that acupuncture was superior to both sham and no acupuncture controls for osteoarthritis pain with effect sizes of 0.16 and 0.57, respectively [18]. The small effect size in trials with sham acupuncture controls may be due to the following reasons: (1) the meta-analysis excluded outlying studies showing a very large effect size [18] and (2) according to Macpherson H, Vickers AJ, et al. in the same research group, acupuncture has a smaller effect size in trials with needle-insertion sham controls than in trials with needle non-insertion sham or non-sham controls [15]. Our previous study was consistent with their findings that acupuncture trials with needle non-insertion controls lead to more positive conclusions than those with needle-insertion sham controls [16]. In the present study, we will use needle non-insertion as the control, which may produce a smaller, nonspecific effect compared to needle-insertion sham controls. However, it should be noted that the effect size estimated from our pilot study [29] is larger than that of the previous study by Vickers AJ et al. [18]. If the power estimates prove to be high, the trail can be used to determine a more accurate effect size for future power calculations.

This trial will expand our knowledge of whether sinew acupuncture will reduce pain intensity, improve the symptoms and movements of KOA patients, and improve QOL. If this study is successful, the effectiveness of sinew acupuncture may be studied using a pragmatic trial design.

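### Blinded assessors ask for each subject's treatment guess and the reason for it at week 4, before the same role carries out the week-6 and week-10 assessments

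*Protocol article*

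**What the plan says.** The abstract and the Study design section call the trial patient- and assessor-blinded, and the Discussion repeats it: "The subjects and assessors will be blinded to subjects’ allocations".

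The section on blinding success gives the end-of-treatment question to that same role: "The blinding success of subjects will be evaluated by assessors after the last treatment session at week 4". The question is "Which acupuncture do you think you received", with three possible answers: sinew, sham or uncertain. It continues: "Those who answered either sinew acupuncture or sham acupuncture will be asked to provide a reason for that assumption; the results will be recorded".

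The Measurement instruments section then gives assessors the later measurements. TUG and the 8-step SCT are "evaluated by assessors at baseline, every 2 weeks after the last treatment session, and at week 6 and week 10". For the SF-36: "The QOL will be collected by assessors at baseline, week 4 and week 10". The Outcome measures section has independent assessors perform the VAS assessments, and Table 1 continues these at weeks 6 and 10. WOMAC is filled in by the subject.

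The article names no separate interviewer for the blinding question, no sealed or self-completed answer, and no fresh assessor for follow-up.

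**The concern.** The article is not silent on who asks the question. It assigns it to the role whose blindness the design claims, and it does so before that role's last two assessment visits.

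A bare guess carries little information. A reason can carry more, because the two arms differ in whether the needle goes through the skin. An assessor told of penetration, blood or a bruise may form a view of the allocation and carry it into weeks 6 and 10.

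At stake is detection bias at the only two visits that show whether any benefit lasts beyond treatment. TUG and SCT are the most exposed, because assessors both evaluate them and accompany the subject, so encouragement or timing could shift. Once data collection has ended, this criticism cannot be answered by analysis.

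**Working it through.** No figure in the plan bears on this point, so the check sets the sections side by side and counts what follows the question.

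**1. Order of events.** The question falls after session 10 in week 4. Table 1 places the follow-up visits at weeks 6 and 10, so everything measured there comes after it.

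**2. Can a reason hint at allocation?**
- Sinew arm (Interventions): the needle goes through the skin and is advanced 10 to 20 mm beneath it.
- Sham arm (Interventions): the needle touches the point but does not pass through the skin.
- Potential risks and management: slight bleeding or bruising is an occasional effect of needling, and bruises usually fade in 2 to 3 days.

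A subject who cites penetration, blood or a bruise is therefore describing something more likely in one arm than the other. Bandages cover the points at the session, and a bruise would usually have gone by week 6. The spoken reason is thus a route that the plan's other blinding measures do not close.

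**3. Who gives a reason?** Everyone is asked for a guess. Only those who name a treatment are asked why; those who answer uncertain are not.

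**4. What comes after the question (Table 1, Outcome measures, Measurement instruments)?**

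| Outcome | Visits after the question | Assessor's part | Count |
|---|---|---|---|
| TUG | weeks 6, 10 | evaluates | 2 |
| 8-step SCT | weeks 6, 10 | evaluates | 2 |
| VAS | weeks 6, 10 | administers; subject marks the scale | 2 |
| SF-36 | week 10 | collects; subject reports | 1 |
| WOMAC | weeks 6, 10 | completed by the subject | not counted |

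Total: 2 + 2 + 2 + 1 = 7 instrument-visits per subject. Four (TUG and SCT) are evaluated by the assessor. The other three (VAS twice, SF-36 once) are reported by the subject and leave less room for influence.

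**5. Is the primary outcome exposed?** The primary outcome is the VAS at week 4. Measurement instruments places the VAS before each session and immediately after it, whereas the blinding question is only placed somewhere after the last session. The pre-session VAS certainly precedes the question, and the natural reading puts the post-session VAS first too. The order of the question relative to TUG, SCT and SF-36 at the week-4 visit is not stated.

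**The case against.** The strongest reply is that a guess is not the allocation. Subjects are themselves blinded by the trolley table, by bandages in both arms and by matched procedures, so the assessor hears only a blinded person's belief. Sensation separates the arms poorly: the sham needle is also felt at the point, and the real needling is shallow and meant not to hurt. This stands, and it limits the conclusion to a possibility. It does not remove the point, because the arms still differ in penetration and the plan makes the assessor ask for the reason.

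A second reply is that the text speaks of assessors in the plural and never says that one individual sees a given subject at weeks 4, 6 and 10. That is true, and rostering is a detail that an article may leave out. But the protocol gives both tasks to one role, and nothing in it keeps the tasks apart.

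Third, TUG and SCT are performance tests with limited room for judgement, and they are secondary outcomes. That also stands and bears on the weight of the point.

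A reader might go further in three ways that the documents do not support:
- That the guess could contaminate the primary VAS. The timing of the VAS immediately after the session speaks against this.
- That having to state a guess colours the subject's own later reports. The documents give no evidence for this, and sealing the answer would not prevent it.
- That the credibility scale raises the same problem. Its four items ask about belief in the treatment and its logic, not about which treatment was received.

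**Conclusion.** The point holds as an avoidable risk of detection bias at follow-up. A stated procedure is at odds with a stated design property. The exposure is seven instrument-visits per subject, chiefly the four TUG and SCT measurements at weeks 6 and 10.

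The conclusion rests on two assumptions: that some subjects give a reason that differs between arms, and that the person who hears it may also assess that subject later. The documents confirm neither and exclude neither. They give no figure for how many subjects would offer a telling reason, so neither the number of compromised assessments nor the size of any bias can be stated.

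It would be too strong to say that assessor blinding is broken, or that the week-4 primary result is in doubt. This is a cheap improvement that protects the secondary follow-up results, not a threat to the main conclusion.

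**What to change.** In the section on blinding success, replace the assessor's interview with a form that the subject completes alone. It would carry the same question, the same three options and the space for a reason. State that it is filled in after all week-4 outcomes have been taken, which also settles its order relative to TUG, SCT and SF-36 at that visit. State that it is then sealed, and that assessors do not see it until week-10 data collection is complete.

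Self-completion is feasible because inclusion criterion (v) requires subjects to read and write Chinese. The cost is one form and a short wording change, with no extra staff or visit, and the blinding data are kept. The small downside is that some free-text reasons may be blank or less detailed than in an interview. The credibility scale can stay as it is.
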